**Methods/design:**

This is a two-arm cluster randomized controlled trial with an estimated sample size of 1088 residents and 74 care staff from eight for-profit private nursing homes. Eligible nursing homes will be those classified as category A2 homes in the Enhanced Bought Place Scheme (EBPS), having a capacity of around 130–150 beds, and no structured PU prevention protocol and/or programmes in place. Care staff will be health workers, personal care workers, and nurses who are front-line staff providing direct care to residents. Eight nursing homes will be randomly assigned to either an experimental or control group. The experimental group will be provided with an intensive training programme and will be involved in the implementation of a 16-week pressure ulcer prevention protocol, while the control group will deliver the usual pressure ulcer prevention care. The study outcomes are the pressure ulcer prevention knowledge and skills of the care staff and the prevalence and incidence of pressure ulcers. Data on the knowledge and skills of care staff, and prevalence of pressure ulcer will be collected at the base line, and then at the 8^th^ week and at completion of the implementation of the protocol. The assessment of the incidence of pressures will start from before the commencement of the intensive training course to the end of the implementation of the protocol.

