### Hypotheses

The experimental group will have a lower incidence and prevalence of PUs than the control group at the end of the implementation of the protocol.The care staff in the experimental group will have more PU knowledge than the care staff in the control group at the 8^th^ week, and at the end of the implementation of the protocol.The care staff in the experimental group will have higher-level PU prevention skills than the care staff in the control group at the 8^th^ week, and at the end of the implementation of the protocol.

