### Interventions

The interventions for both the experimental and control groups pertain to the cluster level and the individual participant level.

In the control group, the care staff will provide residents with the usual PU prevention care, which is a series of personal care activities that include perineal care, the repositioning of residents, skin moisturization, and the sitting out of residents.

The experimental group will be involved in the implementation of the comprehensive PU prevention programme, the aim of which is to equip care staff with PU prevention knowledge and skills, and to guide care staff including HWs and PCWs, in PU prevention. This programme is the same as the previous programme that was pilot tested [8, 9]. It consists of two major components: an intensive training course (a two-hour lecture and two skill-training sessions) and a PU prevention protocol.

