### Study outcomes and measures

The primary outcomes are the incidence and prevalence of pressure ulcers. The secondary outcomes are the care staff’s knowledge and skills on preventing pressure ulcers. These outcomes will pertain to the cluster and individual participant levels.

PU incidence and prevalence: The incidence of PUs will be assessed using the validated PU incidence form [6]. The form will record the numbers, locations, and stages of the PUs that are detected. The common PU sites are numbered from 1 to 36 on a body map. The identification of stages will be adopted from the guidelines of the European Pressure Ulcer Advisory Panel and the National Pressure Ulcer Advisory Panel [7]. The prevalence of PUs will be evaluated using the validated prevalence form [6].

PU prevention knowledge: In this study, the knowledge test, which demonstrated good internal consistency and content validity, [8] will be adopted to assess the care staff’s knowledge of PU. The test has 30 true-false items, with each correct answer allocated a score of one. The range of scores is from 0 to 30, and the total score is 30. A higher score indicates a higher level of knowledge of PU.

PU prevention skill level: The skill checklist, which has good content validity and internal consistency, [8] will be used to assess the care staff’s skills on turning, positioning, transferring, lifting, and use of materials/devices for preventing pressure ulcers. The checklist lists the steps required to demonstrate the five different skills and the rating for the performance of the skill in each step using a 4-point scale: unsatisfactory (1), barely satisfactory (2), satisfactory (3), and very satisfactory (4). A higher total score indicates better skill at preventing PUs.

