### Study procedures

The four trained RAs, who are registered nurses and will be blind to the group allocation, will collect the data. Each RA will be responsible for collecting the data for two nursing homes. The following data will be collected from both the experimental and control groups (Table 1). Immediately before (T0) the lecture, at the 8^th^ week (T1), and at the end of the implementation (T2) of the protocol (at the 16^th^ week of the implementation of the protocol), the staff participants will be assessed on their knowledge on preventing pressure ulcers in the presence of the RAs. Before the commencement of the skill training (T0), at the 8^th^ week (T1), and at the end (T2) of the implementation of the protocol (T3), the RAs will conduct an individual assessment of the staff participants’ skills on turning, positioning, transferring, lifting, and the use of preventive materials, while they are performing daily care for residents.

**Table 1 Tab1:** Data collection

Study outcomes	Before the lecture	Before the skill training	Immediately before commencement of protocol implementation	8^th^ week after the protocol	At the end of the protocol
Knowledge	✓			✓	✓
Skills		✓		✓	✓
Prevalence	✓		✓	✓	✓
Incidence “-------------------------------the whole period					

In assessing the incidence of PUs, the RAs will inspect the skin of each resident two times a week to detect the first PUs (on residents without PUs) and new PUs (on residents already suffering from PUs), starting from before the intensive training course to the end of the implementation of the protocol. The size, location, and stage of PUs will be assessed when they are detected. The prevalence of PUs will be evaluated by the RAs before the commencement of the intensive training course (T0), immediately before the commencement of the implementation of the protocol (T1), at the 8^th^ week (T2), and at the end (T3) of the implementation of the protocol. An inter-rater agreement of at least 90 % among four RAs will be obtained for the skill checklists and PU assessment (size, location, and stage) before the skill-training sessions.

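### Primary ulcer incidence is counted from before the training course, so it includes ulcers that precede any part of the programme, and the counting window has no defined start in control homes

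*Protocol article*

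**What the plan says.** Study outcomes and measures sets the endpoint: "The primary outcomes are the incidence and prevalence of pressure ulcers".

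The counting window is given three times, consistently:
- Study procedures has research assistants inspect every resident's skin twice a week for first and new ulcers, "starting from before the intensive training course to the end of the implementation of the protocol".
- The Abstract (Methods/design) says that the assessment "will start from before the commencement of the intensive training course to the end of the implementation of the protocol".
- Table 1 marks incidence as running over "the whole period".

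Statistical analysis compares incidence between groups with a chi-square test and mentions no other window. The hypothesis is "The experimental group will have a lower incidence and prevalence of PUs than the control group at the end of the implementation of the protocol".

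On the intervention, the Interventions section says: "It consists of two major components: an intensive training course (a two-hour lecture and two skill-training sessions) and a PU prevention protocol". The course is given in the four experimental homes only, and control homes continue usual care. Table 1 applies to both groups, but its columns are named after the lecture, the skill training and the protocol. Prevalence is surveyed before the course and again immediately before the protocol starts, so the plan itself treats these as different times.

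**The concern.** Before the first lecture both arms receive usual care, so ulcers arising then carry no information about the programme. Counted as primary events, they raise the risk in both arms by about the same amount and shrink the relative contrast.

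The second issue is the anchor. Cumulative incidence grows with time under observation, so a comparison of proportions is fair only if both arms are watched for the same time. The window is tied to the course and the protocol, which control homes do not have, and the article gives them no date or week instead. At stake are some lost power and, if observation times turned out to differ, a biased primary comparison.

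**Working it through.** **Inputs.** Risks of 9.5 % and 6 %, 80 % power, significance level 0.05 and 355 residents per group come from Sample size. The 16-week protocol period comes from Interventions. The length of the lead-in L is not in the article, so 1, 2 and 4 weeks are assumptions.

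**The plan's own figures.** The odds ratio is (0.06/0.94)/(0.095/0.905) = 0.61, close to the stated 0.60. For the group size, with the mean risk p̄ = 0.0775,

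n = [1.96·√(2·p̄·(1−p̄)) + 0.8416·√(p₁(1−p₁) + p₂(1−p₂))]² / (p₁−p₂)² = (0.7412 + 0.3176)² / 0.035² ≈ 915 per group, two-sided.

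The stated 355 per group does not reproduce. That is a separate matter, and this point does not depend on it. To keep the two apart, the loss is shown relative to 915.

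**Dilution model.** Take 9.5 % and 6 % as 16-week risks with constant hazards:
- control: h₁ = −ln(0.905)/16 = 0.00624 per week
- experimental, from protocol start: h₂ = −ln(0.94)/16 = 0.00387 per week

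With L unaffected weeks counted first in both arms:
- control risk = 1 − exp[−h₁(16 + L)]
- experimental risk = 1 − exp[−h₁L − 16h₂]
- lead-in share of experimental events = (1 − exp[−h₁L]) / experimental risk

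| L (weeks) | Control | Experimental | Risk ratio | Lead-in share of experimental events | n per group for 80 % |
|---|---|---|---|---|---|
| 0 | 9.5 % | 6.0 % | 0.63 | 0 % | 915 |
| 1 | 10.1 % | 6.6 % | 0.65 | 9 % | 989 |
| 2 | 10.6 % | 7.2 % | 0.67 | 17 % | 1064 |
| 4 | 11.7 % | 8.3 % | 0.71 | 30 % | 1214 |

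Relative to 915, restoring 80 % power takes 8 %, 16 % or 33 % more residents (989/915, 1064/915, 1214/915). Without them, a design with 80 % power at L = 0 would have about 77 %, 74 % or 68 %.

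**Other readings of 9.5 %.** If it is the control risk over the whole window, with the same hazard ratio during the protocol weeks, the experimental risk becomes 6.2 %, 6.4 % or 6.7 %. The risk ratios are again 0.65, 0.67 and 0.71. If the source study used the same window with a similar lead-in, its 9.5 % and 6 % already contain the dilution, and nothing is lost against the plan.

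**Why the control start matters.** Suppose the programme had no effect and control homes were watched one week longer than 16. The risk ratio would then be 0.095/0.1006 = 0.94 from observation time alone. Nothing in the article says that this will happen.

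**The case against.** **Training is intervention.** A reader might infer that all time before protocol day 1 is pre-intervention. The Interventions section does not support this, because the course is one of the programme's two components. Only the time before the first lecture is strictly pre-intervention, and it may be short. This stands, and it limits both the claim and the fix.

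**Unequal windows.** A reader might also infer that control homes have a different start and that the comparison is therefore biased. The documents do not show this. Both groups follow Table 1, and all homes are randomized together once recruitment is complete, so a shared calendar is possible. What stands is that no control-home start is defined.

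**Surveillance is not analysis.** The inspection schedule need not be the counting rule, the planned GEE of ulcer status over time could use early findings as baseline, and a fuller document could fix the window. But incidence is a primary outcome, its window is stated three times without a split, and the chi-square test has no other window attached. The article states a rule here; it does not leave one out.

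**Whole-programme counting is pragmatic and at worst conservative.** It is true that dilution is expected to run towards no difference. But intention-to-treat concerns who is analysed and in which arm; it does not require counting events that precede the intervention.

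**Size.** The lead-in is unknown, and at one week the shift from 0.63 to 0.65 is small. This stands.

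**Conclusion.** The point holds in limited form. Followed as written, the plan counts ulcers that arose before any part of the programme was delivered, which dilutes a primary comparison, and it defines the window by events that occur in one arm only. The expected direction is towards no difference, not in favour of the programme.

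The size is conditional. The risk ratio moves from 0.63 to about 0.65–0.71 if 1 to 4 unaffected weeks are counted, the hazard is constant, and 9.5 % and 6 % are 16-week risks free of lead-in. A shorter lead-in gives less, and a source study with the same window gives no loss against the plan. Any effect of training before the protocol starts would also reduce the loss, because the model treats all lead-in weeks as unaffected. Bias from unequal observation time is possible but not shown.

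**What to change.** - **Primary definition.** Count residents with at least one new ulcer from a single common start to the end of week 16. The start is the date of the first training session in the experimental homes, and the same calendar start and length apply to control homes.
- **Baseline.** Use ulcer findings before that date only as baseline, with each resident's ulcer status at T0 (before the course) as a covariate in the GEE.
- **No adjustment for incidence after training begins.** Training may already have changed it. For the same reason, the primary count should not start at protocol day 1, which would drop outcomes that arise after the intervention has begun.
- **Secondary analyses.** Report the count from protocol day 1 to week 16, and the whole-period count.

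The cost is one reworded definition and a recorded start date for each control home. The twice-weekly inspections already supply the data. The downside is slightly fewer counted events.

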### Sample size

In a previous study, [9] the incidence of PUs dropped from 9.5 % to 6 % after the implementation of the programme, corresponding to an odds ratio of 0.60 [7, 8]. Based on these figures, 710 residents (355 per group) will be required for 80 % power at a significance level of 0.05. Assuming an intra-cluster correlation of 0.1 %, a total of 784 (392 per group) will be required. Based on a previous study, [8] we allow for a 20 % drop-out rate and a 90 % resident recruitment rate. We will thus need 1088 residents from eight for-profit NHs (544 residents per group). The capacity of each home should then be around 130 to 140. Based on a similar PU prevention programme for care providers [8] that increased staff knowledge and skills with a Cohen’s d of 0.95 and 1.13 respectively, a total of at least 36 care staff (18 per group) will be required to achieve 80 % power at a significance level of 0.05. Allowing for a 30 % drop-out rate and a 70 % staff recruitment rate, [8]. We estimated that at least 74 care staff (37 per group) from eight nursing homes will be required for this study.

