### Randomization

Randomization will be carried out after the written informed consent of all individual residents to participate this study has been obtained and the recruitment of residents from the eight nursing homes has been completed. The PI will assign each nursing home that has agreed to join the study a number of from one to eight. A trained RA using the random number generator will randomly assign four numbers to the experimental group and the remaining four numbers to the control group. In accordance with the randomized numbers, the PI will assign the eight nursing homes to the experimental or control groups.

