### Statistical analysis

IBM SPSS Statistics 22 will be used to analyse the data. An intention-to-treat analysis will be adopted. Descriptive statistics such as mean or percentage will be used to summarize PU prevention knowledge and skills, and the prevalence and incidence of PUs. A chi-square test will be performed to compare the PU prevalence and PU incidence of residents between the two groups. An independent t-test will be adopted to compare the knowledge and skills of care staff between the two groups. Generalized estimating equation (GEE) will be used to compare the two groups in terms of their performance in the knowledge and skills tests, as well as in PU status over time, and to examine the groups by the time interaction effect, adjusting for the cluster effect and possible confounders. Significance will be set at a P value of < =0.05.

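### The 355 residents per group do not follow from 9.5 % versus 6 %: about 915 per group are needed, and the stated 80 % power is really about 41 %

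*Protocol article*

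**What the plan says.** The Sample size section of the protocol article takes its planning effect from a previous study in which "the incidence of PUs dropped from 9.5 % to 6 % after the implementation of the programme", "corresponding to an odds ratio of 0.60". It then states: "Based on these figures, 710 residents (355 per group) will be required for 80 % power at a significance level of 0.05".

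The section then raises the total to 784 (392 per group) for an intra-cluster correlation of 0.1 %, and to 1088 (544 per group) for 20 % drop-out and 90 % recruitment. It derives a home capacity of around 130 to 140 from that. The abstract repeats the result: "an estimated sample size of 1088 residents and 74 care staff from eight for-profit private nursing homes".

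Two other sections fix the remaining inputs. Under Randomization, a research assistant will "randomly assign four numbers to the experimental group and the remaining four numbers to the control group", so allocation is 1:1. Under Statistical analysis, "A chi-square test will be performed to compare the PU prevalence and PU incidence of residents between the two groups" and "Significance will be set at a P value of < =0.05". Study outcomes and measures names incidence, with prevalence, as primary.

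**The concern.** A difference of 3.5 percentage points between two rates below 10 % normally needs many hundreds of residents per group, so 355 looked far too small for 80 % power. The section gives every input except the sidedness of the test, so the figure can be checked directly.

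Incidence is a primary outcome, and the 9.5 % versus 6 % calculation is the only one given for residents. If the starting number is wrong, so are 784, 1088 and the required home size. The trial would then run on a belief in 80 % power while having less than an even chance (two-sided) of detecting the effect it was planned for. A non-significant result could be taken as evidence that the programme does not work.

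**Working it through.** **Inputs**

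- Control incidence p1 = 0.095 and experimental incidence p2 = 0.06 (Sample size).
- Power 80 %, significance level 0.05 (Sample size).
- Equal groups (Randomization); chi-square comparison (Statistical analysis).
- Sidedness is not stated. I take two-sided, the natural reading of a chi-square test at 0.05, and show one-sided as well.

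**Odds ratio.** (0.06/0.94) / (0.095/0.905) = 0.608. This agrees with the stated 0.60 to rounding, so the odds ratio does not explain the gap.

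**Required size.** With mean rate p = 0.0775 and pooled variance under the null,

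n per group = [z_α √(2p(1−p)) + z_β √(p1(1−p1) + p2(1−p2))]² / (p1−p2)²

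- √(2 × 0.0775 × 0.9225) = 0.3781
- √(0.095 × 0.905 + 0.06 × 0.94) = 0.3773
- Two-sided: (1.96 × 0.3781 + 0.8416 × 0.3773)² / 0.035² = 1.1208 / 0.001225 = **915 per group**
- One-sided: (1.645 × 0.3781 + 0.8416 × 0.3773)² / 0.035² = 0.8827 / 0.001225 = **721 per group**

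The stated 355 is not reproduced. Other standard formulas do not reach it either:

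| Method, n per group | Two-sided | One-sided |
|---|---|---|
| Pooled variance | 915 | 721 |
| Unpooled variance | 912 | 719 |
| Arcsine | 905 | 713 |
| Continuity-corrected | 972 | 777 |
| Odds ratio exactly 0.60 (p2 = 0.0593), pooled | 874 | 688 |

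Across all two-group variants tried, including log-odds-ratio and Poisson forms, the smallest was 672 per group (one-sided arcsine, odds ratio exactly 0.60 against 6 %).

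**Power at 355 per group.**

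Power = Φ{[0.035 √n − z_α × 0.3781] / 0.3773}

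- Two-sided: (0.6595 − 0.7411) / 0.3773 = −0.216, power **41.4 %**. A simulation of the chi-square test with 200,000 runs gave 41.8 %.
- One-sided: (0.6595 − 0.6220) / 0.3773 = 0.099, power **54.0 %**.

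**Do the later steps restore power?** They are broadly consistent with each other: 784/710 = 1.104 as the implied design effect; 392 / (0.8 × 0.9) = 544; 2 × 544 = 1088; 1088/8 = 136 residents per home. Working back from 544:

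- Analysed: 544 × 0.8 × 0.9 = 392 per group, or 392/4 = 98 per home.
- Design effect: 1 + 97 × 0.001 = 1.097.
- Effective size: 392/1.097 = 357 per group, power 41.7 %.

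Ignoring clustering, 392 per group gives 45 %. Even if all 544 per group were analysed with no clustering, power would be 58 %.

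**What 355 per group can detect.** Holding p1 at 9.5 % and solving the same formula for 80 % two-sided power gives p2 = 4.2 %, an odds ratio of about 0.42.

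**Size after clustering.** At 98 analysed per home, 915 × 1.097 = 1,004 analysed per group, which implies about ten homes per arm (1,004/98). Keeping four homes per arm, the homes and the design effect must grow together: 4 × 915 × 0.999 / (4 − 0.915) = 1,185 analysed per group, and 1,185/0.72 = about 1,646 per group before the drop-out and recruitment losses. The plan has 392 and 544.

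**The case against.** **Sidedness.** The protocol does not state it, and the hypotheses are directional. On a one-sided reading power is 54 %, so the statement that it lies below one half is tied to the two-sided reading. That qualification stands. A chi-square test at 0.05 points to two-sided, and a one-sided test still needs about twice 355 per group.

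**An unstated assumption.** The Statistical analysis section plans generalized estimating equations for ulcer status over time. A repeated-measures gain with three or four measurements and a within-resident correlation of roughly 0.08 to 0.18 would bring 915 down to about 355. But the sample-size paragraph bases its number on two incidence proportions and claims no such gain, and the gain would not apply to incidence accumulated over the whole period and compared by chi-square. This supports offering the sponsor the chance to state a missing assumption; it does not make the sentence correct.

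**A higher control rate.** The Background cites 25 % incidence in four other private homes. At 25 % and an odds ratio of 0.60, about 372 per group would suffice. So 41 % is the power for the effect the protocol planned on, not a forecast of realised power. The paragraph nevertheless uses 9.5 %.

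**Few homes.** Testing on a t distribution with 6 degrees of freedom (4 + 4 homes − 2) would lower power further, to about 31 to 32 %. The protocol does not name such a test, so I give this as a side note only.

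**Cause.** The stated total of 710 is close to the one-sided per-group size (713 to 721), so a per-group figure may have been used as a total. This is a guess, and nothing depends on it.

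**Conclusion.** The concern holds: the sample-size statement is wrong as written. For 9.5 % versus 6 % at 80 % power and a two-sided 0.05 level, about 915 residents per group are needed before clustering, and 355 is 39 % of that (355/915). Power for the planned effect is about 41 to 42 %, whether taken at 355 per group or at the 357 effective residents per group that the full plan delivers. If the test were one-sided, the figures are 721 per group and 54 %.

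The conclusion rests on the protocol's own rates, 1:1 allocation, its intra-cluster correlation of 0.001 and its drop-out and recruitment allowances. The only assumption added is the two-sided test, and relaxing it reduces the error without removing it. The error carries into 784, 1088 and the home capacity.

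**What to change.** Rewrite the resident part of the Sample size section so that it:

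- states that 9.5 % versus 6 % needs about 915 residents per group (two-sided 0.05, 80 % power) before clustering, and names the sidedness;
- states that the planned 784 analysed residents (392 per group, intra-cluster correlation 0.001) give about 42 % power for that effect, and, if a test on 6 degrees of freedom is adopted, about 32 %;
- states the effect detectable with 80 % power, about 9.5 % versus 4.2 %;
- removes the claim of 80 % power for 9.5 % versus 6 %. If an undocumented assumption produced 355, state and justify it instead;
- commits to reporting the incidence effect with its confidence interval and to not reading non-significance as absence of effect.

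If the sponsor prefers to keep 80 % power for the original effect, the size must be recalculated. With four homes per arm that is about 1,185 analysed per group; at 98 analysed per home it is about 1,004 per group, with more homes.

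The correction itself costs only rewording and a less favourable stated power. It requires no additional residents.

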## Background

The world is ageing and the population of older adults is growing quickly [1]. Hong Kong is also facing the challenge of an aging population. In mid-2013, 14.3 % of Hong Kong’s total population consisted of people aged 65 or above [2] and this figure is predicted to rise markedly to 19 % in 2021 and 26 % in 2031 [3]. Nursing homes are the last resort for older people who are at an advanced age and/or frail. The current demand for government-subsidized residential care homes (RCHs) is much greater than the supply [4]. Consequently, a large number of older people have turned to for-profit private nursing homes (NHs) [4]. In view of the increasing number of older people and a lack of future planning to ensure an adequate supply of government-subsidized RCHs for older people, the demand for for-profit private NHs will increase rapidly.

However, for-profit private NHs have been criticized for providing substandard care because many potential residents in private NHs cannot afford to pay high fees. To reduce costs in order to make a profit, private NHs employ personal care workers (PCWs) and health workers (HWs) as a large proportion of their care staff to perform the majority of personal care to residents; however, such staff are less educated, experienced, and trained than those in government-subsidized NHs. Furthermore, the departure of non-professional workers in NHs from a sector that is already operating with less than three-quarters of the needed manpower [5] is further harming the quality of the services that are provided. This substandard care is a possible cause of the high incidence of pressure ulcers (PUs) in for-profit private NHs [6]. Hence, PUs are considered a major clinical risk that needs to be managed, especially in for-profit private nursing homes.

A PU is a ‘localized injury to the skin and/or underlying tissue usually over a bony prominence, as a result of pressure, or pressure in combination with shear’ [7]. There are no published data on the prevalence and incidence of PUs in long-term RCHs in Hong Kong, with the exception of three studies [6, 8, 9] that were conducted by the researcher of this article. A PU incidence rate of 25 % was reported in four for-profit private NHs in one district [6] and a 9.5 % rate in three private NHs in another district [9]. The PU incidence rate of 2.5 % that was found in a government-subsidized NH is substantially lower [8].

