### Participant recruitment

The principle investigator (PI) of the study will conveniently select the districts and private NHs and invite those NHs that meet the inclusion criteria to participate in this study. After the confirmation of an NH’s participation in the study, the recruitment of residents and care staff will begin. In recruiting residents and care staff in each NH, the in-charge of each NH will refer the residents and care staff who meet the criteria for inclusion in this study to trained research assistants (RAs), who will confirm their eligibility to participate in this study. Afterwards, the in-charge will arrange a meeting to allow the PI explain the details, benefits, and possible risks of the study to potential staff and resident participants, and to the primary family caregivers of potential resident participants with cognitive impairment. The potential participants will also be provided with information sheets for their information when considering whether or not to participate in this study. Before the commencement of the study, the RAs will obtain the written informed consent of the participants and primary family caregivers of cognitively impaired participants in each nursing home to participate in this study. After the recruitment of staff and resident participants from eight nursing homes has been completed, randomization will be carried out.

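### The intra-cluster correlation of 0.1% is unsourced and optimistic, and with four homes per arm the stated 80% power is not secured

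*Protocol article*

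**What the plan says.** The protocol's Sample size section starts from an earlier study in which "the incidence of PUs dropped from 9.5" % to 6 % "after the implementation of the programme, corresponding to an odds ratio of 0.60". From this it states that "710 residents (355 per group) will be required for 80" % power at a significance level of 0.05. Then, "Assuming an intra-cluster correlation of 0.1" %, the total becomes 784 (392 per group). After 20% drop-out and 90% recruitment it becomes 1088 residents in eight homes. The effect size, drop-out and recruitment figures carry references; the ICC carries neither a reference nor a reason.

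The Background section gives two rates for private for-profit homes: "A PU incidence rate of 25" % in four homes of one district, and a 9.5 % "rate in three private NHs in another district". Only the 9.5% is carried into the sample size.

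Under Participant recruitment, the investigator "will conveniently select the districts and private NHs". The Randomization section allocates eight homes 4:4 by random number and mentions no stratification.

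**The concern.** Incidence of pressure ulcers is a primary outcome, and only eight units are randomised. In such a design, power depends mainly on how much homes differ from one another, and adding residents within homes soon stops helping. An ICC of 0.001 says that homes hardly differ, which is why the allowance for clustering costs only about 10% more residents.

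That picture sits badly with the protocol's own account of the sector, where two sets of private homes are reported 15.5 percentage points apart. Since homes may come from several districts and allocation is not stratified, any district difference becomes part of the between-home variation in this trial. If the ICC is larger than assumed, a null result would be read against a claimed 80% power that the design does not have.

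**Working it through.** **Inputs.** ICC 0.001; incidence 9.5% and 6%; base 355 per group; 392 analysed per group in four homes, so 392/4 = 98 per home (all from Sample size). 25% in four homes and 9.5% in three (Background). Two-sided 5% is assumed, because the section does not state sidedness.

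**1. The protocol's clustering step.** Design effect DE = 1 + (m − 1) × ICC. With m = 98: DE = 1 + 97 × 0.001 = 1.097, and 710 × 1.097 = 779. With m = 105 the result is 784. Then 784/(0.8 × 0.9) = 1089, against 1088 stated. The steps from 710 to 784 to 1088 are therefore sound; the issue is the ICC put into them.

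**2. What ICC 0.001 means.** Between-home SD = √(ICC × p(1 − p)) = √(0.001 × 0.095 × 0.905) = 0.0093, or 0.93 percentage points. The 95% range of home rates is 9.5% ± 1.96 × 0.93, about 7.7% to 11.3%. The gap of 15.5 points in the Background is about 17 such SDs.

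**3. What the two Background rates would suggest if read as home rates.** With four homes at 0.25 and three at 0.095, the mean is 0.184. The between-home variance is 0.0059 (divisor 7) or 0.0069 (divisor 6), and p(1 − p) = 0.150. The ratio is 0.039 to 0.046. Treating the two rates as two single points gives 0.084. The spread shows how weakly these figures fix a value.

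**4. Power on the protocol's own base.** Grant that 355 effective residents per group give 80%. The noncentrality is then (1.960 + 0.842) × √(ESS/355), with ESS = 392/DE. The normal column uses 1.960 as critical value. The t column uses the noncentral t with 8 − 2 = 6 df (critical value 2.447), because eight homes are randomised.

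| ICC | DE | ESS per group | Power, normal | Power, t (6 df) |
|---|---|---|---|---|
| 0.001 | 1.097 | 357 | 80% | 65% |
| 0.005 | 1.485 | 264 | 68% | 53% |
| 0.01 | 1.97 | 199 | 55% | 42% |
| 0.02 | 2.94 | 133 | 40% | 30% |
| 0.04 | 4.88 | 80 | 27% | 20% |

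**5. Ceiling with four homes per arm.** ESS = 4m/(1 + (m − 1) × ICC), which tends to 4/ICC as m grows. Setting 4/ICC = 355 gives ICC = 0.0113. Above that value, 355 effective residents per group cannot be reached at any home size.

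**6. A separate fault in the base.** For 9.5% versus 6% at 80% power, two-sided, n = [1.960√(2 × 0.0775 × 0.9225) + 0.842√(0.095 × 0.905 + 0.06 × 0.94)]²/0.035² = 915 per group. A one-sided test still needs 721. The stated 355 per group does not reproduce either way. With the noncentrality taken directly from the two rates, 392 per group gives 45% at ICC 0 (normal). With the design effect included, power (normal / t on 6 df) is 42%/32% at ICC 0.001 and 26%/20% at 0.01.

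**The case against.** A reader might infer that the Background rates contradict the ICC of 0.001, or show it to be some 40 times too small. The document does not support that. The 25% and 9.5% are pooled figures from two separate studies. Their follow-up, denominators, case-mix and per-home rates are not given, and cumulative incidence grows with follow-up. Under a constant hazard, follow-up ln(0.75)/ln(0.905) = 2.9 times as long would turn 9.5% into 25% with no difference between homes. The trial also restricts itself to category A2 homes of similar size without a prevention protocol, which may narrow the variation. Even the home count of the second study is uncertain: the Background says three and the Interventions section, citing the same reference, says four. All of this stands, and it reduces 0.04 to an illustration.

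A reader might also blame clustering for the 42% at ICC 0.001. That would be wrong: at ICC 0 the figure is already 45%, so nearly all of the shortfall from 80% belongs to the base of 355. Step 4 keeps the two faults apart for this reason.

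The Sample size section names neither a formula nor a reference distribution, so it cannot be said that the sponsor used a normal reference. The t column shows only what eight randomised units allow.

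Finally, the Statistical analysis section already plans GEE with adjustment for clustering and possible confounders. That provides for adjustment in the analysis but does not support the power claim.

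**Conclusion.** The concern holds as a lack of support and not as a contradiction. The ICC of 0.001 is unsourced and implies homes that are nearly identical. Nothing in the protocol supports this, and its own sector figures make it look optimistic.

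The conclusion does not need 0.04. On the protocol's own base, an ICC of 0.01 lowers power to 55% (normal) or 42% (6 df). Even at 0.001, allowing for eight randomised units gives 65%. The separate error in the base lowers true power further at every ICC.

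These figures assume a two-sided 5% test, 98 analysed residents in every home and no gain from covariates. The ICC range of 0.001 to 0.04 is itself an assumption. The issue is one of precision and of the claim made for it; it does not bias the treatment comparison.

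**What to change.** - Replace the single ICC with a justified range, for example 0.001 to 0.04, preferably drawn from per-home data of the earlier studies. Report power for four homes per arm on 6 df and withdraw the 80% claim. Correct the base of 355 per group in the same revision.
- Name T0 pressure ulcer prevalence as an adjustment covariate in the primary comparison. It is already collected before training starts. Do not use pre-implementation incidence: that count runs through the training course, which is one of the programme's two components, so adjusting for it could remove part of the effect.

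The cost is a less favourable stated power, and a home-level covariate uses one of the 6 df. No new data are needed. Adjustment may recover some precision but may not restore 80%, and only more homes would lift the ceiling directly. On the protocol's own base and a normal reference, ICC 0.01 would need 355 × 1.97/98 = 7.1, so eight homes per arm.
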